## Abstract

**Background:**

Globally, nurses are facing increased pressure to provide high-quality complex patient care within environments with scarce resources in terms of staffing, infrastructure, or financial reward. The strain and demand on the psychological health and well-being of nurses during COVID-19 has been substantial, with many experiencing burnout; as such, interventions to enhance resilience within the workplace are required. A face-to-face resilience enhancement training program for nurses that was effective in improving resilience levels was translated into a 4-week online training program, Resilience Enhancement Online Training for Nurses (REsOluTioN), to enable greater accessibility for nurses.

**Objective:**

This study aims to compare levels of resilience, psychological health, and well-being in nurses before and after the online resilience training compared to a wait list control group. It will also explore participants’ engagement with the trial and their acceptability of the online training.

**Methods:**

This is a two-arm, parallel, randomized controlled trial with a 6-week follow-up period. Up to 100 registered nonagency nurses working at a National Health Service hospital trust in South England will be recruited. Four cohorts will run, and participants will be randomized into a wait list control group or to REsOluTioN. Pre- and postonline surveys will collect study outcome measure data. In the REsOluTioN arm, data will be collected on the perceived usefulness of the online training via an online survey. Institutional and health research authority approvals have been obtained.

**Results:**

REsOluTioN will aim to empower nurses to maintain and enhance their resilience while working under challenging clinical conditions. The online training will be interactive with input from mentors, health care leaders, and peers to promote engagement and enhanced communication, and will create a forum where nurses can express their views and concerns, without hierarchical infrastructures inhibiting them. This can increase self-knowledge and learning around workplace resilience coping strategies and provide a safe space to validate feelings through mentorship and peer support. Findings will be reported in accordance with the CONSORT (Consolidated Standards of Reporting Trials) guidelines. The trial is now finished and was conducted between August 2021 and May 2022.

**Conclusions:**

The REsOluTioN trial will enable preliminary data to be gathered to indicate the online training’s effectiveness in enhancing nurses’ resilience in the workplace, with the potential for larger scale follow-up studies to identify its value to nurses working across a range of health care settings.

**Trial Registration:**

ClinicalTrials.gov NCT05074563; https://clinicaltrials.gov/ct2/show/NCT05074563

**International Registered Report Identifier (IRRID):**

DERR1-10.2196/37015

## Introduction

Worldwide, nurses are facing increased pressure to provide high-quality complex patient care to patients within environments with scarce resources in terms of staffing, infrastructure, or financial reward [1,2]. The constant strain and demand placed on nurses working in highly pressurized and often unsafe conditions, and a lack of career structure or progression means many registered nurses’ resilience levels are tested due to stress and burnout [2-4]. This stress has intensified over the last couple of years due to the COVID-19 pandemic with nurses supporting the delivery of expert patient care and rapidly responding to substantial health care challenges [1]. While nurses’ contribution to keeping the public safe and protecting the National Health Service (NHS) in the United Kingdom during COVID-19 has been widely recognized, the resulting psychological impact on health and well-being has been substantial; resilience enhancement interventions are one way to tackle this growing problem within health care services [5-8].

The NHS has been facing increased pressure due to the pandemic conditions it is being subjected to [9]. This, in addition to the chronic pressures in terms of staffing, sickness, infrastructure, and financial problems, means that nurses are facing increased pressure [2] and are experiencing burnout, as they struggle to cope with the never ceasing demands of their job roles, which are in continuous high demand [4]. The NHS Health and Wellbeing Framework [10] sets the standards for how NHS organizations should support staff to feel well, healthy, and happy at work, and advocates for the delivery of evidence-based staff health and well-being plans [10]. Resilience-building programs [11-14] are recognized as important in contributing to increased psychological health and well-being in nurses as well as aiding recruitment and retention within international health care organizations [15,16].

Recent literature has recommended that resilience-building initiatives, including mentorship programs outside of nurses’ immediate workplace settings, are incorporated into nursing education, as well as specific self-development strategies to help enhance personal resilience [15]. Resilience programs have been found to build and enhance nurses’ resilience and can also support recruitment and retention for health care workers [16]. This has been evidenced in a number of recent workplace resilience enhancement interventions within nursing [17-22].

As a result of the need for targeted resilience enhancement interventions within the nursing setting, a UK-based resilience enhancement program was developed [22,23]. A detailed description of the theoretical background of the program is available elsewhere [22]. This face-to-face program targets four core components to improve the ability of the nurses to bounce back from day-to-day problems and to remain resilient in the workplace: workplace hardiness, emotional intelligence, critical thinking, and achieving life balance and enabling spirituality. These components were informed by a 2014 integrative review [15] that reported difficult workplace situations, feelings of emptiness, and a diminishing sense of inner balance as main contributing factors for resilience in nurses. Various strategies such as reflecting on emotions, interactions and guidance from peers and mentors, and skills to develop work-life balance and toughening up are shown to be helpful in building resilience.

The program consisted of six sessions with nurses that covered topics including building hardiness, maintaining a positive outlook, achieving work-life balance, reflective and critical thinking, and enabling spirituality [22,23]. In addition, one-to-one mentor sessions were provided over a 12-week period; senior nurse leaders within the participating trust took on these mentorship roles [23]. The face-to-face program was evaluated using pre- and postsurveys and interviews with nurses. Findings showed that nurses’ resilience levels were significantly higher after the training, with reported positive impacts on personal resilience, self-awareness, confidence, well-being, and professional and team-working relationships [22]. As a result, a wider rollout of the training was proposed. However, this planned rollout was disrupted by the onset of the COVID-19 pandemic due to social-distancing measures, making the face-to-face training untenable.

Due to the restrictions imposed by COVID-19, the face-to-face training program [22,23] was adapted and transformed to online training as a means of increasing accessibility for all nurses who were no longer able to attend face-to-face training. The online training was also informed by a recent systematic review examining the effectiveness of online interventions to enhance resilience in health care professionals ([name], unpublished data, 2022) and focus groups with nurses to gather information on what they felt should be key features of an online resilience training program. An online format was felt necessary due to its potential to be rolled out widely to all nurses working in health care settings due to ease of accessibility, flexible access, and a decreased need for other resources such as physical space and in-person facilitation. The online resilience training, entitled Resilience Enhancement Online Training for Nurses (REsOluTioN), is relevant in the COVID-19 climate, where consideration about how to optimize the experiences of the nursing workforce and the resulting impacts on patient care are urgently needed.

In light of the above, the randomized controlled trial described in this paper aims to pilot REsOluTioN, an online resilience training for nurses working during COVID-19. Specific study objectives are:

To compare levels of resilience, psychological health, and well-being in nurses who complete REsOluTioN with nurses who do not (control arm)To explore participant engagement with the trial and acceptability of REsOluTioNTo collect feedback on various components of REsOluTioN

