## Methods

### Study Design

The study is a two-arm, parallel-group, individually randomized pilot trial comparing REsOluTioN versus a wait list control group. The study flowchart describing the study process is presented in Figure 1. The study schedule of events and assessments are presented in Figure 2.

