### Sample Size

Given the study objective to afford a preliminary comparison of training outcomes, as well as funding constraints and the pressures imposed by COVID-19, we propose to recruit a minimum of 60 and up to 100 participants. We aim to recruit participants over four cohorts with approximately 25 participants per cohort.

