### Allocation

After providing online consent, participants will be randomized to receive either the wait list control or REsOluTioN on a 1:1 ratio. An independent research staff not involved in the design and conduct of the trial will generate a computer-generated random number sequence. Allocation concealment will be upheld using sequentially numbered opaque-sealed envelopes that will be opened sequentially only after entering the name of each participant on the envelope. A research team member who is not involved in the delivery of REsOluTioN or data analysis will implement the group allocation and contact participants to inform them of their group allocation.

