#### Training Outcomes

##### Acceptability of REsOluTioN

Data will be collected on the number of registered nurses who complete REsOluTioN, discontinued in between, and did not complete the posttraining survey to estimate the acceptability of REsOluTioN.

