### Statistical Methods

Demographic characteristics of the study participants will be descriptively summarized. The proportion of participants who enrolled, completed the study, provided follow-up data, or discontinued the study, and those responding to each category on the Likert-type closed questions in the survey will be reported. Pre- and postsurveys on resilience and psychological well-being will be presented as means (SDs) or medians (IQRs) depending on the normality as per Shapiro-Wilk test. The differences in resilience and psychological well-being within each arm and between arms at 6 weeks will be assessed using analysis of variance. A significance level of 0.05 will be considered. All analysis will be undertaken in SPSS statistics software, version 22.0 (IBM Corp) [26].

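### Objective 1 defines the trained group by completion of REsOluTioN, which conflicts with the by-arm comparison stated elsewhere and, taken literally, is not a randomized comparison

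*Protocol article*

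**What the plan says.** The list of specific objectives in the Introduction opens with "To compare levels of resilience, psychological health, and well-being in nurses who complete REsOluTioN with nurses who do not (control arm". The trained group is named by completion, and the parenthesis fixes the comparator as the control arm.

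Four other places describe the comparison by arm:
- The Abstract's Objective speaks of outcomes "in nurses before and after the online resilience training compared to a wait list control group".
- Study Design calls this an "individually randomized pilot trial comparing REsOluTioN versus a wait list control group".
- Allocation says that "participants will be randomized to receive either the wait list control or REsOluTioN on a 1:1 ratio".
- Statistical Methods states: "The differences in resilience and psychological well-being within each arm and between arms at 6 weeks will be assessed using analysis of variance".

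The section on acceptability treats completion as separate from allocation. It counts the "number of registered nurses who complete REsOluTioN, discontinued in between, and did not complete the posttraining survey". The Control Arm section gives wait-list nurses the study materials only after their 6-week survey, so they have no training to complete during the comparison period.

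**The concern.** Completing the training happens after randomization and can happen in only one arm. A nurse randomized to REsOluTioN who stops part-way is not a completer and is not in the control arm, so objective 1 read literally places her in neither group. All controls stay in, including those who would have stopped had they been offered the training. The two groups are then no longer alike by design.

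If completing is related to the resilience or well-being that a nurse would have had at 6 weeks anyway, the contrast shows a difference even when the training does nothing. The likely direction is in favour of the training: the Introduction describes nurses under heavy strain, and Time Commitment asks for 10 hours plus 4-8 hours of mentor meetings, so the most strained may be the likeliest to stop. That is a judgement, not something the documents report.

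The Discussion makes a larger national trial depend on whether the programme looks effective, so the contrast behind that statement should be a randomized one.

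**Working it through.** **The protocol's own figures.** Sample Size states "we propose to recruit a minimum of 60 and up to 100 participants", over "four cohorts with approximately 25 participants per cohort". The maximum reproduces: 4 x 25 = 100. With 1:1 allocation that is 50 per arm, and the minimum of 60 is 30 per arm. No power, effect size, SD or completion rate is given, so there is no further figure to reproduce. The significance level is 0.05 (Statistical Methods); two-sided testing is assumed.

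**Simple check (all inputs assumed).** Suppose 30% of the REsOluTioN arm do not complete, would score 0.5 SD below completers, and the training has no effect.
- Bias of completers versus all controls = non-completion share x gap = 0.30 x 0.5 = 0.15 SD.
- With 50 per arm, completers number 0.70 x 50 = 35. The standard error is sqrt(1/35 + 1/50) = 0.220 SD.
- Noncentrality = 0.15 / 0.220 = 0.68. Two-sided rejection at 1.96 is about 0.105, against a nominal 0.05.
- Over 20-40% non-completion and a gap of 0.3-0.5 SD, the bias runs from 0.20 x 0.3 = 0.06 to 0.40 x 0.5 = 0.20 SD.

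That range fixes the sign in advance, so a second model lets the sign vary.

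**Second model.** Let c be the completion rate and rho the correlation between a latent tendency to complete and the 6-week score. With no training effect,

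bias in SD = rho x phi(t) / c, where t = z(1 - c) and phi is the standard normal density.

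Example: for c = 0.70, t = -0.524, phi(t) = 0.348 and phi(t)/c = 0.497. With rho = 0.3 the bias is 0.149 SD, in line with the simple check.

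Each cell gives the bias in SD, then the false-positive rate with 50 per arm. The rates come from 20,000 simulated trials per cell, comparing completers with all controls by pooled t statistic with cut-off 2.0.

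| Completion | rho = -0.3 | rho = 0 | rho = 0.1 | rho = 0.3 | rho = 0.5 |
|---|---|---|---|---|---|
| 90% | -0.058; 0.058 | 0; 0.047 | 0.019; 0.048 | 0.058; 0.057 | 0.097; 0.071 |
| 80% | -0.105; 0.078 | 0; 0.049 | 0.035; 0.050 | 0.105; 0.074 | 0.175; 0.125 |
| 70% | -0.149; 0.102 | 0; 0.050 | 0.050; 0.054 | 0.149; 0.098 | 0.248; 0.203 |
| 60% | -0.193; 0.134 | 0; 0.046 | 0.064; 0.055 | 0.193; 0.127 | 0.322; 0.283 |

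The bias does not depend on sample size. With 30 per arm the false-positive rates are mostly lower; the largest is 0.184, at 60% completion and rho = 0.5.

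**Comparison as allocated.** With complete follow-up, all randomized nurses compared by arm give zero bias under no effect and a false-positive rate of 0.05, whatever c and rho are.

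**The case against.** The best defence is that objective 1 is shorthand for the two arms. Much of this stands:
- Statistical Methods compares arms and does not mention completion. The Abstract and Study Design read the same way.
- The article uses completion loosely elsewhere. Time Commitment assumes that those randomized to REsOluTioN will have finished the 10 structured hours, and Data Collection Methods awards the certificate to those randomized, after the post-survey, with no completion test.
- No completion threshold is defined, so a completer filter could not be applied as written.
- Data Collection Methods gathers both scales from participants in both arms. Nothing stops the 6-week survey for nurses who leave the training.
- A full definition of the analysis set may sit in an analysis plan that is not shown, so its absence is no fault here.

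A reader might therefore be tempted to infer that the trial will drop non-completers, or that its result is bound to favour the training. The documents support neither. The first would need an analysis passage that restricts the REsOluTioN arm, and there is none. The second would need a completion rate and a link between completing and outcome, and neither is given.

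The defence does not remove the conflict. The acceptability section separates completing from discontinuing, and Perceived Usefulness refers to nurses by randomization when allocation is meant, so both terms were available. A comparison between arms could be run on completers or on everyone randomized, and nothing in the article says that nurses are analysed as allocated. A published objective that names a non-randomized contrast should not stand on the hope that it will be read as shorthand.

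**Conclusion.** The point holds as an inconsistency between objective 1 and the by-arm comparison in the Abstract, Study Design and Statistical Methods. Followed literally, the objective excludes REsOluTioN nurses who discontinue and is no longer a randomized comparison. That loss does not depend on the direction of any bias.

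Size and sign rest wholly on assumed inputs. For 60-90% completion and a correlation of 0.1 to 0.5, the bias is about +0.02 to +0.32 SD and the false-positive rate about 0.05 to 0.28 with 30-50 per arm. At zero correlation there is no bias; at -0.3 and 70% completion it is -0.15 SD, against the training. Bias towards the training is plausible if strained nurses drop out, but it is not established.

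This is a pilot offering a preliminary comparison, and its analysis section already points to arms. The correction is well worth making, but the documents do not show a biased analysis.

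**What to change.** 1. Reword objective 1 as a comparison of nurses randomized to REsOluTioN versus nurses randomized to the wait list.
2. Add one line to Statistical Methods: the between-arm comparison at 6 weeks includes all randomized nurses with a 6-week score, in their allocated arm, whatever amount of training they completed.
3. Label any comparison of completers with controls as supplementary and non-randomized.

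The cost is two lines of wording, and the estimate may be slightly less favourable to the training. The Results section says that the trial has finished, so the change bears on analysis and reporting; further follow-up of nurses who stopped may no longer be possible. The change does not deal with nurses who returned no 6-week survey. Their number should be reported by arm, since selective non-response could bias the as-allocated comparison too.

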## Methods

### Study Design

The study is a two-arm, parallel-group, individually randomized pilot trial comparing REsOluTioN versus a wait list control group. The study flowchart describing the study process is presented in Figure 1. The study schedule of events and assessments are presented in Figure 2.

**Figure 1 figure1:**
[figure not shown]
Study flowchart. NHS: National Health Service. REsOluTioN: Resilience Enhancement Online Training for Nurses. CPD: continuing professional development.

**Figure 2 figure2:**
[figure not shown]
Schedule of study events and assessments. REsOluTioN: Resilience Enhancement Online Training for Nurses.

### Eligibility Criteria

Any registered nonagency nurses working at any level of seniority and across any clinical setting at the participating trust will be eligible to participate. All participants must be able and willing to provide online informed consent.

### Recruitment

Nurses will be recruited through study advertisement posters and promotional videos hosted on the trust website, social media platforms, and trust premises. The researchers will attend nurse-led meetings across the trust to promote the study and will contact managers from different specialties including children, adult, and older people’s services. The researchers will also work with the hospital communications team who will include information about the study in their weekly news bulletins. The study has been endorsed by the NHS trust’s chief nurse who will be asked to share information about the trial to all nurses working in the trust, using email communications and online meeting forums. The trust’s research delivery teams will also promote the study to the clinical teams they work with. These multiple recruitment methods are deemed necessary due to the ongoing pressures facing nurses due to the pandemic, making recruitment likely to be challenging. A web link with study information included within it will be shared with people who express an interest in taking part. They will then be directed to a web page containing the online study information sheet and consent form, prior to any data collection or study procedures being undertaken. Once online consent has been confirmed, participants will be asked to complete a prestudy survey (Figure 2).

### Sample Size

Given the study objective to afford a preliminary comparison of training outcomes, as well as funding constraints and the pressures imposed by COVID-19, we propose to recruit a minimum of 60 and up to 100 participants. We aim to recruit participants over four cohorts with approximately 25 participants per cohort.

### Allocation

After providing online consent, participants will be randomized to receive either the wait list control or REsOluTioN on a 1:1 ratio. An independent research staff not involved in the design and conduct of the trial will generate a computer-generated random number sequence. Allocation concealment will be upheld using sequentially numbered opaque-sealed envelopes that will be opened sequentially only after entering the name of each participant on the envelope. A research team member who is not involved in the delivery of REsOluTioN or data analysis will implement the group allocation and contact participants to inform them of their group allocation.

### Blinding

Participants will not be blinded to their group allocation and will complete self-reported online surveys at the start of the study and after 6 weeks. It is not possible to blind the team member who undertakes the allocation assignment; however, other research team members who analyze the pre-post survey responses will be blinded to treatment allocation.

### Patient and Public Engagement

This trial evaluates an online resilience training developed for nurses and was informed by the feedback provided by nurses in the previous face-to-face training and a systematic review [22,23] ([name], unpublished data, 2022).

